## 1.8 Exploratory endpoints

Cervical dilatation rate, calculated as a function of time (functional data)

Indication for operative delivery:

1. Labor dystocia (defined in Stimulering av rier/Langsom framgang i fødsel [eHåndbok]),
2. In first stage: If the action line is crossed, amniotomy should be performed (The Partogram has an alert and an action line. The alert line marks 1 cm per hour and the action line is 4 hours shifted to the right of this). After amniotomy, wait at least 1 hour before augmenting with oxytocin stimulation. If progress in birth await oxytocin. If the water is already broken when slow progress occurs, oxytocin infusion should be started.
3. Fetal distress (non-reassuring fetal heart rate tracing as defined in Fosterovervåkning under fødsel [eHåndbok])

|               |                                                                                                       |                                        |                                                            |
|---------------|-------------------------------------------------------------------------------------------------------|----------------------------------------|------------------------------------------------------------|
| Avvikende CTG | 100-110 slag/min                                                                                      | > 25 slag/min
(saltatorisk mønster) | -Ukompliserte variable
deselerasjoner
(slagtap > 60) |
|               | 150-170 slag/min

-Kort bradycardiepisode:
<100 slag/min for > 3 min
<80 slag/min > 2 min | < 5 slag/min > 40 min                  |                                                            |

| En kombinasjon av 2 eller flere avvikende faktorer gir et patologisk CTG |                                                                                                                         |                                                |                                                                                                            |
|--------------------------------------------------------------------------|-------------------------------------------------------------------------------------------------------------------------|------------------------------------------------|------------------------------------------------------------------------------------------------------------|
| Patologisk CTG                                                           | >170 slag/min

-Bestående bradycardi:
<100 slag/min i > 10 min
<80 slag/min i > 3 min uten stigende tendens | < 5 slag/min i > 60 min
Sinusoidalt mønster | -Kompliserte variable deselerasjoner: varer > 60 sek.

-Tilbakevendende sene uniforme deselerasjoner |
| Preterminalt CTG                                                         | Fravær av variabilitet < 2 slag/min eller reaktivitet med eller uten deselerasjoner eller bradycardi                    |                                                |                                                                                                            |

#### 4. Other indications

Maternal heart rate: Continuous registration at least 30 minutes from IMP is given.

Fetal heart rate: Continuous registration at least 30 minutes from IMP is given.

## 2 OVERALL STUDY DESIGN

The study is a double-blind, randomized placebo-controlled trial

|                     |                                                       |
|---------------------|-------------------------------------------------------|
| Study Period        | Estimated date of first patient enrolled: June 1 2019 |
|                     | Anticipated recruitment period: 24 months             |
|                     | Estimated date of last patient completed: May 31 2021 |
| Treatment Duration: | One dose of Investigational Medical Product (IMP)     |
| Follow-up:          | 1 month                                               |

## **3 STUDY POPULATION**

### **3.1 Selection of Study Population**

Academic hospital in Norway. Primiparous women who are giving birth at Department of Obstetrics Rikshospitalet, Oslo University Hospital are invited to participate.

The women will be invited approximately six weeks prior to their due date (gestational week 30), and will receive a mailed invitation letter. In the letter, they will be given opportunity to actively opt out of inclusion. At this time, women may give informed consent to participate, or they can be included when they arrive at the delivery ward. All women will have the opportunity to talk to a midwife or doctor before they give written informed consent, and contact information will be provided in the invitation. The Principal Investigator will sign the consent form.

Women who have received and understood information about the study and are willing to participate prior to start of labor may be included and sign the informed consent form when they arrive at the hospital to give birth.

### **3.2 Number of Patients**

A maximum number of 250 patients will be included in this trial.

### **3.3 Inclusion Criteria**

All of the following conditions must apply to the prospective patient at screening prior to receiving study agent:

- $\geq 18$  years
- Primiparous women
- Spontaneous onset of labor
- Active phase of labor
- $\geq 37$  weeks of gestation
- Vertex position
- Crossing the alert line, i.e.: cervical dilatation of less than one cm per hour in the active phase of first stage of labor (cervix dilation  $\geq 3$  -  $<10$  cm)

### **3.4 Exclusion Criteria**

Patients will be excluded from the study if they meet any of the following criteria:

- Multiple gestation
- Elective cesarean section

- Women in labor receiving oxytocin before start of active labor ( cervix: 3 cm)
- Fully dilated cervix when crossing the alert line
- Preeclampsia defined as blood pressure  $\geq 140/90$  and proteinuria (+1 or more on a urine dipstick on more than one occasion) with debut after 20 weeks of pregnancy
- Previous major uterine surgery
- Known intestinal stenosis, ileus or megacolon
- Persisting maternal tachycardia (heart rate  $>130$  beats per minute)
- Known maternal myasthenia gravis
- Persisting fetal tachycardia (fetal heart rate baseline  $>170$  beats per minute)
- Hypersensitivity to any of the ingredients in 'IMP or placebo (butylscopolamine bromide or sodium chloride).
- Women with heart disease who are under surveillance with heart rate monitoring during labor
- Known fetal heart disease
- Untreated glaucoma

## 4 TREATMENT

For this study Butylscopolamine Bromide and placebo (sodium chloride) are defined as the Investigational Medicinal Product (IMP).

### The intervention group

Women randomised to the intervention group will receive 20 mg Butylscopolamine bromide (20mg/ml) intravenously when they cross the alert line of the partogram, In addition they will be given standard care, i.e. augmentation with oxytocin as per ward procedure. If there is indication for Buscopan and oxytocin at the same time, both drugs can be given simultaneously.

### The control group

Women randomised to the control group will receive saline solution 1 ml intravenously when they cross the alert line of the partogram, In addition they will be given standard care, i.e. augmentation with oxytocin as per ward procedure.

## 4.1 Drug Identity, Supply and Storage

Drug: Butylscopolamine Bromide (Buscopan), Boehringer Ingelheim, 20 mg/mL. 1 mL contains Butylscopolamine Bromide 20 mg, sodium chloride 6 mg and water.

Placebo: Sodium chloride 1 mL (Natriumklorid “Fresenius Kabi” oppløsningsvæske til parenteral bruk 9mg/mL).

The placebo and drug preparations will be visually identical – both are colorless fluids.

We refer to the storage and preparation instructions on the package leaflet.

## 4.2 Dosage and Drug Administration

IMP will be given, as soon as possible after it is noticed that a woman has crossed the alert line, as one dose of 1 mL (butylscopolamine bromide 20 mg/mL or placebo) intravenously.

To our knowledge, no dose finding studies have been performed on laboring women. The RCTs that have been performed have mostly used 20 mg iv. There is one unpublished study that used 40 mg iv, and one RCT that used 40 mg rectal dose. There is not enough data to perform complete comparisons between 20 mg iv and 40 mg iv, but so far 20 mg iv seems to be as effective as 40 mg iv when the measure of effect is duration of active phase of labor and the Buscopan is administered routinely in all laboring women (please see table).

| Author (ref)    | Dose (mg) /adm | Points Cochrane * | Country      | Journal               | N/parity    | Time difference (minutes) |
|------------------------|-----------------------|--------------------------|---------------------|------------------------------|--------------------|----------------------------------|
| Al Qahanti (32) | 40 mg im       | 5                 | Saudi Arabia | Ther Clin Risk Manag. | 97/ para 0  | 50                        |
| Makvandi (33)   | 20 supp        | 4                 | Iran         | Croat Med Journ       | 130/ para 0 | 89                        |

|                     |                 |                                        |                |                                                  |                      |                   |
|---------------------|-----------------|----------------------------------------|----------------|--------------------------------------------------|----------------------|-------------------|
| Mukaiindo    | 40 mg iv | 7                               | Kenya   | unpublished                               |                      |                   |
| Samuels (34) | 20 iv    | 7                               | Jamaica | BJOG                                      | 129/mix       | 72         |
| Sekhvat (35) | 20 iv    | 3                               | Iran    | African Health Science                    | 188/multipara | 74         |
| Kirim (26)   | 20 iv    | Published after Cochrane review | Turkey  | Journal of Maternal, Fetal and Neon. Med. | 387/mix       | 57 minutes |

The study treatment will be administered to the woman by authorized site personnel only.

IMP must be given as soon as possible after randomization. If IMP is given more than 45 minutes after randomization, the midwife must check the cervical dilatation again before IMP is given.

The intravenous injection should be performed 'slowly' (in rare cases a marked drop in blood pressure and even shock may be produced by Buscopan).

### 4.3 Duration of Therapy

Patients will receive one dose of IMP, 1 mL intravenously. All other treatment is given according to ward procedures.

### 4.4 Schedule Modifications

### 4.5 Concomitant Medication

All concomitant medication (incl. vitamins, herbal preparation and other “over-the-counter” drugs) used by the patient will be recorded in the patient’s file and CRF. Several drugs may enhance the anticholinergic effect of butylscopolamine and should not be administered during labor. These include:

Antihistamines

Tricyclic and tetracyclic antidepressants

Antipsychotic drugs

Other anticholinergic drugs (tiatropium, ipratropium, atropine)

Metoclopramide

Beta-adrenergic medications may give tachycardia

## **4.6 Participant Compliance**

Compliance with medications is recorded by the midwife in charge. Given that the IMP is administered intravenously, compliance is not expected to be a problem.

## **4.7 Drug Accountability**

The responsible site personnel will confirm receipt of study drug and will use the study drug only within the framework of this clinical study and in accordance with this protocol. Receipt, distribution, return, and destruction (if any) of the study drug will be properly documented on a list in the locked room, and in the medical record.

## **4.8 Drug Labeling**

The IMPs will have standard labeling from the manufacturer including package insert until it is prepared by the unblinded study personnel.

The IMPs will be ordered from the hospital pharmacy's general drug supply according to the same procedures as for any patient who is given treatment with one of these drugs. The unblinded midwife who prepares the solution for intravenous injection will record the batch number and expiry date from the original drug package, write the information on the randomization sheet, and put it back into the envelopes used for randomization. The midwife thereafter closes and seals the envelopes. The envelopes are kept in the locked room in case of the need for unblinding. The batch number and expiry date will be recorded next to the participant number, which will be used for the respective solution for intravenous injection and recorded on the label used for the final solution for intravenous injection.

The solution container will be labeled with the following information:

- The name of the study
- The name of the Principal Investigator
- Department of Obstetrics
- "Buscopan or saline for iv injection"
- Participant number

## **4.9 Participant Numbering**

Each woman is identified in the study by a unique participant number that is assigned when the woman signs the Informed Consent Form. Once assigned the participant number cannot be reused for any other woman.

## 5 STUDY PROCEDURES

### 5.1 Flow Chart

**Table 1. Trial flow chart**

|                                                          | Screening Period | Delivery                                                                       |              |                           | End of maternity ward stay |                                 | Follow-up evaluation |
|----------------------------------------------------------|------------------|--------------------------------------------------------------------------------|--------------|---------------------------|----------------------------|---------------------------------|----------------------|
| Time                                                     |                  | Baseline
( $\geq 3$ cm and $< 10$ cm dilatation)
Crossing the alert line | IMP is given | 30 min after IMP is given | Day of delivery            | Day of discharge                | 1 month postpartum   |
| Informed consent                                         | X                |                                                                                |              |                           |                            |                                 |                      |
| Inclusion/exclusion Evaluation                           | X                |                                                                                |              |                           |                            |                                 |                      |
| Medical History                                          | X                |                                                                                |              |                           |                            |                                 |                      |
| Concomitant Medication                                   | X                | X                                                                              |              |                           |                            |                                 |                      |
| a Physical Examination fetus (CTG)            |                  | X                                                                              | X            | X                         |                            |                                 |                      |
| b Vital signs mother                          |                  | X                                                                              | X            |                           | X                          | X                               |                      |
| Cervical dilatation                                      |                  | X                                                                              |              |                           |                            |                                 |                      |
| Pain measurement (VAS)                                   |                  |                                                                                | X            | X                         |                            |                                 |                      |
| Treatment administration                                 |                  |                                                                                | X            |                           |                            |                                 |                      |
| Adverse event, mother                                    |                  |                                                                                | X            | X                         | X                          | X                               |                      |
| Adverse event, newborn/fetus                             |                  |                                                                                | X            | X                         | X                          | X                               |                      |
| c Physical Examination newborn (pediatrician) |                  |                                                                                |              |                           |                            | 1 st day post partum |                      |
| Questionnaire (Delivery experience)                      |                  |                                                                                |              |                           |                            |                                 | X                    |

aPhysical Examination fetus (CTG) includes continuous fetal heart rate tracing.

bVital signs mother include blood pressure and pulse. Maternal height and body weight will be obtained from the pregnancy chart.

cPhysical Examination newborn will include an examination of general appearance

## **5.2 By Visit**

### **Informed consent**

All participating women will sign an informed consent during pregnancy. They will receive the invitation to participate in the study six weeks before their due date if they are primiparous, planning a vaginal delivery, and are going to give birth at Oslo University Hospital Rikshospitalet. The laboring women and their fetuses will be monitored after inclusion using CTG (cardiotocography) and measurement of the maternal heart rate for 30 minutes after the treatment is initiated. Patient reported side effects (maternal) will be registered in the CRF based on a list of symptoms. Occurrence, degree and duration of side effects will be registered within 30 minutes after the treatment is given. Treatment of side effects will be registered. All women will be asked to assess labor pain before initiation of the treatment, and 30 minutes after initiation of the treatment, as well as to fill in a validated questionnaire on birth experience one month after delivery.

Informed consent must have been given voluntarily by each woman before any study specific procedures are initiated. The following data will be retrieved from the participants' medical charts and pregnancy charts:

### **Clinical status**

Maternal medical history (including disease history and corresponding treatment details), weight, blood pressure and pulse. Fetal cardiotocography (at least 10 minutes if not already recorded).

### **Concomitant medication**

All concomitant medication used by the woman within 7 days of treatment start must be recorded in the CRF. Concomitant medication will also be recorded at randomization

### **Physical examination fetus**

The physical examination of the fetus includes continuous fetal heart monitoring with ST-analysis and will be recorded from the administration of IMP and 30 minutes after the administration, if any abnormal heart rate is discovered, the fetal heart rate will be monitored until delivery.

### **Physical examination newborn**

Umbilical cord pH from the umbilical artery and vein will be obtained immediately after delivery. Pulse oximetry with O2 saturation will be performed 4 hours after delivery. Physical examination of the newborn will be performed on the first or second day postpartum by an experienced pediatrician from the neonatal intensive care unit. All newborns will be observed by trained personnel at the maternity ward throughout the stay.

### **Physical examination mother**

Includes heart rate and blood pressure

### **Cervical dilatation**

Will be examined immediately before randomization (after the woman has crossed the alert line of the partogram), when IMP is given (if there is more than 45 minutes between randomization and IMP). After IMP is given the midwife will examine the cervix according to ward routine, but at least every two hours.

**Questionnaire** Childbirth experience questionnaire (CEQ) developed and validated in Sweden consists of 22 items in 4 categories: own capacity, professional support, perceived safety and participation. We have added one question concerning request for caesarean section in next pregnancy

### **Pain measurement**

Pain before and after administration of IMP will be self-reported on a visual analogue scale.

### **Adverse events**

Adverse events will be recorded for both mother and fetus after 30 minutes after IMP is given, on the first day after delivery and at discharge from the maternity ward.

### **Eligibility criteria**

All eligibility criteria should be assessed together with relevant baseline parameters prior to study inclusion (inclusion/exclusion criteria), and eligibility should be confirmed in the inclusion chart.

#### **5.2.1 Before Treatment Starts**

- Eligibility will be assessed by the inclusion chart
- Baseline is defined as the time point in labor when slow progress is detected. At baseline, vital signs from mother and fetus will be obtained, and we will perform baseline observations regarding medical history
- For the endpoint pain baseline measurements by a VAS scale will be obtained before randomization

#### **5.2.2 During Treatment**

All treatment events take place during labor. Eligible women will receive one dose of IMP . Efficacy is assessed by cervical dilation (measured at least every two hours), time to delivery, dose and time of oxytocin treatment needed and mode of delivery. Efficacy regarding pain is assessed by VAS scale measurements 30 minutes after initiation of IMP.

Toxicity is assessed by maternal vital signs (continuous heart rate measurements) and continuous fetal heart rate tracing.

Other treatments for labor arrest will be offered to the participants as per ward procedure. These treatments include artificial rupture of membranes and intravenous oxytocin infusion.

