| Efficacy Assessments: | Time from start of intervention to delivery. Mode of delivery. Dose and time of oxytocin treatment needed. |
| Safety Assessments:   | Fetal heart rate. Maternal heart rate.                                                                     |
| Other Assessments:    | Pain during labor. Experience of labor and birth.                                                          |

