Maternal: Common ( $\geq 1/100$  to  $< 1/10$ ): Gastrointestinal: Dryness in the mouth. Cardiology: Tachycardia, dizziness. Ophtalmology: Accomodation disturbance. Unknown frequency: Cardiology: Hypotension, flushing. Skin: Dyshidrosis. Immune system: Anaphylactic shock, anaphylactic reactions, dyspnea, skin reactions including urticarial, rash, erythema and itching. Other forms of hypersensitivity. Kidney: Urinary retention. Ophtalmology: Mydriasis, increased intraocular pressure. Rare cases with serious skin reactions like Steven-Johnsons syndrome have been reported.

According to WHO recommendations for augmentation of labor based on the Cochrane review from 2013 (22),(31), there are 5 RCTs comparing Buscopan with placebo including altogether 845 newborns with no differences in transfer to the Neonatal Intensive Care Unit. One RCT with 100 fetuses did not show any differences in prevalence of fetal distress. One RCT with 130 fetuses did not show any difference in fetal bradycardia, and two RCTs with 230 fetuses did not show any difference in fetal tachycardia. None of the 17 RCTs in the Cochrane review reported any side effects related to Buscopan (22).

Women who are allocated to the control group will contribute to answer an important medical question for future laboring women and their children. They will need an IV access, which could be considered a down side. However, it is routine procedure in the hospital to establish an IV line

when there is labor dystocia. The IV access may be an advantage if they women augmentation with oxytocin or if something unexpected happens.

Women who are allocated to the intervention group may experience a shorter labor if the IMP has the presumed effect. In that case, they will receive less oxytocin, and experience fewer oxytocin side effects. Based on previous studies, the reduction in the active phase of labor will be approximately one hour. This reduction will take place in the first stage (opening phase), and not the second stage of labor (expulsion phase).

Based on data from our department, 72% of primiparous women who crossed the alert line (the inclusion criterion of this study) of the partogram received augmentation with oxytocin with an average duration of 214 minutes. Of the women who crossed the alert line, 15% delivered by cesarean section and 25% had an operative vaginal delivery, compared to 2% and 16% among women with normal progress in labor, respectively.

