## **7.4 Recording of Adverse Events**

If the patient has experienced adverse event(s), the investigator will record the following information in the CRF:

- The nature of the event(s) will be described by the investigator in precise standard medical terminology (i.e. not necessarily the exact words used by the patient).
- The duration of the event will be described in terms of event onset date and event ended data.
- The intensity of the adverse event will be described as mild, moderate and severe.
  - Mild; asymptomatic or mild symptoms; clinical or diagnostic observations only; intervention not indicated.
  - Moderate; minimal, local or noninvasive intervention indicated; limiting age-appropriate instrumental Activities of Daily Living.
  - Severe or medically significant but not immediately life-threatening; hospitalization or prolongation of hospitalization indicated.
- Specifically, mild AEs include dryness of the mouth, transient tachycardia and flushing. Moderate AEs include visual disturbances, urinary retention, and fall in blood pressure and skin reactions. SAEs include dyspnea, anaphylactic reactions, serious skin reactions including Steven-Johnson and anaphylactic shock.
- The Causal relationship of the event to the study medication will be assessed as one of the following:

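### The protocol names a fall in blood pressure as a risk of the injection but schedules no clearly post-dose, timed blood pressure before the day-of-delivery column

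*Protocol*

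**What the plan says.** **The risk.** Section 4.2 gives the reason for slow injection: "in rare cases a marked drop in blood pressure and even shock may be produced by Buscopan". Section 1.5 lists among the drug's maternal side effects "Unknown frequency: Cardiology: Hypotension, flushing". Section 7.4 grades examples of adverse events: "Moderate AEs include visual disturbances, urinary retention, and fall in blood pressure and skin reactions".

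**What counts as maternal vital signs.** Footnote b to Table 1 reads "Vital signs mother include blood pressure and pulse". Section 6.2, on safety and tolerability, gives the same definition and refers to the flow chart for timing. Section 5.2 also says that the mother's physical examination includes heart rate and blood pressure, without giving a time.

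**What is monitored after dosing.** The synopsis lists the safety assessments as "Fetal heart rate. Maternal heart rate". Section 5.2 describes CTG and "measurement of the maternal heart rate for 30 minutes after the treatment is initiated". Section 5.2.2 says "Toxicity is assessed by maternal vital signs (continuous heart rate measurements) and continuous fetal heart rate tracing". Sections 1.8 and 6.1 require continuous registration of maternal heart rate for at least 30 minutes from IMP. None of these places names blood pressure.

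**When it is scheduled.** Table 1 ticks maternal vital signs at baseline, at IMP administration, on the day of delivery and on the day of discharge. The 30-minute cell is blank.

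**The concern.** A risk that the protocol itself names should have a matching measurement, or a statement that it is followed through adverse event reports alone. Here the definition of vital signs and section 6.2 point to blood pressure as a safety measurement, while the text on the period after dosing mentions only heart rate. A site cannot tell whether a post-dose blood pressure is due.

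What is at stake is how the safety tables can be read. Under section 9.5.5 safety is described and tabulated only. If few entries for a fall in blood pressure appear, the reader cannot tell a true absence from a fall that caused no symptoms and was not measured. Section 1.2 puts the drug's onset at under 20 minutes. That figure concerns onset in general and is no stated time course for blood pressure, but it makes the first half hour the natural period to ask about, and the protocol already uses that period for its other post-dose assessments.

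**Working it through.** The protocol states no figure on this point, so the check sets its passages side by side.

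**Step 1. Table 1 by column.**

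| Row | Baseline | IMP given | 30 min after | Day of delivery | Day of discharge |
|---|---|---|---|---|---|
| Maternal vital signs (blood pressure, pulse) | X | X | blank | X | X |
| Fetal CTG | X | X | X | blank | blank |
| Pain (VAS) | blank | X | X | blank | blank |
| Adverse events, mother | blank | X | X | X | X |

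Three kinds of assessment are ticked at 30 minutes; maternal vital signs are not. A damaged table does not explain this, because sections 5.2 and 5.2.2 and the synopsis leave out blood pressure independently.

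**Step 2. Is the reading at IMP administration before or after the injection?** The protocol does not say, and other rows in the same column point in different directions.
- Pain is ticked there, and section 5.2 has pain assessed before treatment starts (section 5.2.1 even puts the baseline VAS before randomization). That suggests a pre-dose use of the column.
- Adverse events are ticked there, and section 7.3 starts their collection at the start of study treatment. That suggests use of the column from dosing onward.

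The timing is therefore open.

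**Step 3. Count of blood pressures after the injection and before the day-of-delivery column.**
- If the reading at IMP administration is pre-dose: 0 per woman.
- If it is post-dose: 1 per woman, at no stated interval after the injection.
- Readings that are both clearly post-dose and timed: 0 under either reading.

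**Step 4. What adverse event collection captures.** Section 5.2 registers patient-reported maternal side effects from a symptom list, with occurrence, degree and duration, within 30 minutes. Table 1 collects adverse events in both arms at dosing, at 30 minutes, on the day of delivery and at discharge. A fall with symptoms reaches the database this way. A fall without symptoms needs a measurement.

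**Step 5. What a measurement could and could not show.** With 250 women allocated 1:1 there are about 125 per arm.

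The protocol gives the frequency of hypotension as unknown, so the rates p below are assumptions. The chance of at least one event in the active arm is 1 − (1 − p)^125:

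| Assumed p | Chance of at least one event |
|---|---|
| 1/10,000 | 1.2% |
| 1/1,000 | 11.8% |
| 1/100 | 71.5% |
| 5/100 | 99.8% |

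For a measured continuous change, the mean difference detectable with 80% power at two-sided 5% is (1.960 + 0.842) × √(2/125) = 2.802 × 0.1265 ≈ 0.35 SD.

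Very rare shock could hardly be compared between arms at this size under any schedule. A shift in measured blood pressure could be estimated usefully, but only if it is measured at a common time.

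**The case against.** The strongest reply is that blood pressure is a declared safety assessment in section 6.2, is ticked in the IMP column separately from baseline, and may well be read after the injection. The risk named in section 4.2 is a marked drop or shock. Such an event would largely be noticed, recorded under blinding in both arms and tabulated. This stands, and it rules out several stronger conclusions that a reader might draw.

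- *No woman has a blood pressure between dosing and the day of delivery.* The protocol does not fix when the IMP-column reading is taken, so this cannot be stated as fact.
- *The risk cannot be detected or compared.* A fall in blood pressure is a named adverse event, and solicited and recorded events can be tabulated by arm. What is lacking is a reliable comparison of measured post-dose blood pressure.
- *The gap is about five hours.* The 5.2 hours in section 9.1 is a group mean from another trial (SD 2.8 hours), counted from randomization rather than from IMP, and the day-of-delivery column has no clock time.
- *The blank cell contradicts the 30-minute heart rate requirement.* Continuous registration is specified separately in sections 1.8, 5.2 and 6.1. A blank for the combined blood pressure and pulse assessment does not cancel it.
- *Low counts would mean that nobody looked.* The protocol describes neither routine ward blood pressure practice nor the content of the symptom list, so neither can be assumed to lack it.

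It is also fair to say that a single reading at 30 minutes could miss a brief fall. That limits what such a reading would prove. It does not resolve the mismatch between the passages.

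**Conclusion.** The point holds as a mismatch between a named risk and the measurement schedule. The protocol defines maternal vital signs for safety as blood pressure and pulse, describes post-dose maternal monitoring as heart rate only, leaves the 30-minute cell blank and does not time the reading at IMP administration. The number of clearly post-dose, timed blood pressures before the day-of-delivery column is zero for each of the 250 women.

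The consequence is limited. Clinically evident hypotension would be captured in both arms. A fall without symptoms may be missed, and measured post-dose blood pressure cannot be reliably compared between arms. How often such falls occur is not known from the protocol, so the number missed cannot be estimated. The conclusion rests on Table 1 as reproduced and on the absence of any post-dose blood pressure time elsewhere in the protocol. The primary efficacy analysis is unaffected. The change is worth making because it is cheap and makes the safety tables interpretable.

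**What to change.** Reconcile the synopsis, the injection warning in section 4.2, Table 1 with footnote b, and sections 5.2, 5.2.2, 6.2 and 7.4, so that they agree on whether blood pressure is a post-dose safety assessment. State whether the reading at IMP administration is taken before or after the injection.

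If blood pressure is meant as a post-dose assessment, as section 6.2 implies, record it at an existing post-dose assessment point, for example the 30-minute column where CTG, VAS and adverse events are already collected. Tabulate the change from the pre-dose value by arm, descriptively, in line with section 9.5.5. If it is not meant as one, say so, and note in the safety report that falls in blood pressure were ascertained through adverse event recording only.

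The cost of the first option is one cuff reading per woman, one CRF field and one descriptive table, at a time when other assessments are already being recorded. This concerns data collection only. Any clinical action on a reading stays with the sponsor and ward procedure.
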